## Abstract

**Background:**

Oliguria is a frequent trigger for administering a fluid bolus, but the effect of fluid bolus in improving urine output is inadequately demonstrated. Here, we summarize the protocol and detailed statistical analysis plan of the randomized, controlled RESPONSE trial comparing follow‐up as the experimental group and a 500 mL crystalloid fluid bolus as the control group for oliguria in critically ill oliguric patients.

**Methods:**

Our trial is an investigator‐initiated, randomized, controlled, pilot trial conducted in three ICUs in two centers. We aim to randomize 1:1 altogether 130 hemodynamically stable oliguric patients either to a 2‐hour follow‐up without interventions or to receive a crystalloid bolus of 500 mL over 30 minutes. The primary outcome is the change in individual urine output during the 2‐hour period compared to 2 hours preceding randomization. Doubling of the urine output is considered clinically significant. Additionally, we record the duration of oliguria, physiological and biochemical variables, adverse events, and the incidences of acute kidney injury and renal replacement therapy.

**Conclusions:**

Oliguria is a frequent trigger for potentially harmful fluid loading. Therefore, the RESPONSE trial will give information of the potential effect of fluid bolus on oliguria in critically ill patients.

**Trial registration:**

clinical.trials.gov, NCT02860572.

## INTRODUCTION

1

Fluid bolus therapy is a widely used intervention in the treatment of critically ill patients.^1^, ^2^ Fluid boluses are typically administered in the optimization phase of fluid resuscitation aiming to optimize and maintain adequate organ perfusion by increasing stroke volume.^3^ After hypotension, oliguria (urine output less than 0.5 mL/kg/h) was the most common trigger to administer a fluid bolus.^2^ Albeit oliguria is often seen as a manifestation of inadequate organ perfusion that can be due to hypovolemia, distributive shock, or depressed cardiac function, it can also be a manifestation of early acute kidney injury (AKI).^4^

Regrettably, the response to fluid bolus is currently poorly documented in clinical practice.^2^ A recent systematic review among septic patients found no previous randomized trials comparing the efficacy of fluid bolus therapy to alternative interventions.^1^ Moreover, few observational studies have reported data regarding urine output in response to fluid bolus therapy, and these data suggest no clinically meaningful response.^1^ A retrospective analysis among patients with acute respiratory distress syndrome in a randomized trial comparing conservative vs liberal fluid management found that urine output did not significantly increase within 4 hours after a fluid bolus.^5^ A small observational study among septic shock patients did not find fluid boluses to increase urine output^6^ whereas another study reported urine output to increase approximately by 50% both among patients with oliguria and AKI after a large fluid bolus (median volume 1224 mL crystalloid or colloid).^7^ Additionally, improvement in systemic hemodynamics after fluid bolus has been found to correlate poorly with renal hemodynamics,^7^, ^8^, ^9^, ^10^ further complicating the assessment of potential benefits of fluid bolus in terms of reversing oliguria. Moreover, the effect of fluid bolus on cardiovascular variables is short‐lived among patients in shock^11^, ^12^ suggesting that fluid boluses in the optimization phase of shock are unlikely to improve patient‐centered outcomes.

A typically administered fluid bolus is 500 mL of crystalloid given over 30 minutes,^2^ and fluid boluses may constitute a marked proportion, up to 50%, of the fluid amount administered daily.^6^ A growing body of evidence suggests a poor renal response to fluid bolus,^5^, ^6^ which particularly among oliguric patients translates to an increased risk of fluid accumulation. Moreover, a growing body of evidence shows association of fluid accumulation with increased risk of mortality.^13^, ^14^, ^15^, ^16^

Therefore, in oliguric critically ill patients, clinical equipoise exists in conducting a randomized trial that aims to compare a follow‐up approach without any fluid bolus to standard therapy with fluid bolus (500 mL of crystalloid administered over 30 minutes). We hypothesize that the incidence of doubling of urine output will not differ between the groups to a clinically significant level defined as at least a 20% absolute increase in the number of responders.

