#### Primary outcome

2.11.2

The primary outcome between follow‐up and fluid bolus groups will be adjusted for the two stratification variables^25^ (presence of AKI and presence of sepsis) using two‐tailed logistic regression. Obtained odds ratios (OR) will be converted to risk ratios (RR) with 95% confidence intervals (CI). Additionally, we will report crude event rates and risk ratios.

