### Sample size

2.12

No reliable previous data to inform about the incidence of the primary outcome were available. Among oliguric (urine output <0.5 mL/kg/h for at least 3 hours), hemodynamically stable patients, 50% were considered as renal responders to a fluid challenge that constituted at least one 500 mL crystalloid bolus administered over 15 minutes.^10^ In that study the definition of a positive renal response (post‐bolus urine output over 0.5 mL/kg/h for at least 3 hours) was more liberal than in our trial.^10^ Fluid bolus did not significantly increase urine output among patients with acute respiratory distress syndrome (both oliguric and non‐oliguric).^5^ Therefore, we assume that 30% of patients in the fluid bolus group will be endpoint‐positive. Additionally, we consider 20% absolute difference (which translates to a number needed to treat of 5) as a minimum clinically meaningful difference between the groups to support the use of such a common and inexpensive intervention. Thus, to reach a 20% absolute difference in the primary outcome (30% in the fluid bolus group and 10% in the noninterventional follow‐up group), 62 patients per group will be required to reach 80% power with significance level set at .05 (two‐sided). Considering possible drop‐outs we aim to randomize 65 patients per group to target at least 62 patients per group in the ITT population.

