## DISCUSSION

3

Albeit fluid bolus therapy is frequently used in oliguria to increase urine output, the success of this intervention is largely unknown. The RESPONSE trial will give high‐quality information about the physiological outcomes of fluid bolus therapy given for oliguria in hemodynamically stable patients compared to a follow‐up treatment strategy without additional fluids. Conservative fluid resuscitation strategies especially in septic patients are actively investigated^28^, ^29^ as the evidence regarding harms of fluid overload are being increasingly recognized, especially among patients with AKI.^30^, ^31^ The results of RESPONSE trial will help to assess the potential benefit of fluid bolus therapy, and if no clinically meaningful improvement on urine output or other physiological variables can be demonstrated, will help in avoiding unnecessary fluid loading in the future.

The randomized approach in studying the response of fluid bolus therapy to an alternative intervention is an obvious strength of our study, as the current evidence is based on observational data. Moreover, we are carefully recording data on other fluid input and output, common hemodynamic parameters, acid‐base balance, and blood gases. Thus, we will be able to provide a detailed analysis on the effects of fluid bolus on these parameters as compared to the follow‐up approach. Additionally, we will include a heterogeneous population of critically ill patients with oliguria who have received the initial fluid resuscitation, which will improve the generalizability of our results.

Our trial has some obvious limitations. First, the intervention is not blinded from the clinical team or the investigators due to its nature. Potentially, clinician aware of the patient being in the follow‐up group may give a fluid bolus after the intervention period, and therefore neutralizing the difference between the groups regarding fluid balance. However, we record the details of urine output and fluid therapy until 6 hours post‐randomization to assess the administration additional fluid boluses. Moreover, the trial statistician will be blinded to the group allocation. Second, our trial protocol does not mandate cardiac output monitoring, and therefore, commenting whether patients were hemodynamic fluid responders will not be possible. However, numerous studies have shown that global hemodynamics and renal hemodynamics do not correlate.^7^, ^10^

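### The hypothesis is that responder rates do not differ by 20 absolute points, but the primary analysis is a superiority test on OR/RR with no risk difference, interval or rule against that margin

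*Protocol article*

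**What the plan says.** All references are to the protocol article.

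- **Introduction.** The trial's hypothesis reads: "We hypothesize that the incidence of doubling of urine output will not differ between the groups to a clinically significant level". The level is "defined as at least a 20% absolute increase in the number of responders". This is a claim that no important difference exists, with a numerical margin on the absolute scale.
- **Section 2.12, Sample size.** The same figure returns as the smallest worthwhile effect: "we consider 20% absolute difference (which translates to a number needed to treat of 5) as a minimum clinically meaningful difference". The assumed rates are 30% with bolus and 10% with follow-up, giving 62 per group for 80% power at a two-sided .05 level. This section also says that no reliable earlier data on the incidence were available.
- **Sections 2.11.1 and 2.11.2.** The primary analysis is a two-sided logistic regression at .05, adjusted for AKI and sepsis, and conclusions rest on the ITT analysis. On the effect measure: "Obtained odds ratios (OR) will be converted to risk ratios (RR) with 95% confidence intervals (CI"). Crude event rates and crude risk ratios are added.
- **Section 2.11.3.** Absolute differences with confidence intervals are planned for continuous outcomes. Dichotomous outcomes get crude rates and risk ratios.
- **Discussion.** On how the results will be used: "if no clinically meaningful improvement on urine output or other physiological variables can be demonstrated, will help in avoiding unnecessary fluid loading".

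**The concern.** The 20-point margin appears in the hypothesis and in the sample size, but not in the planned inference. A superiority test asks whether the difference is distinguishable from zero. The hypothesis asks whether the difference is smaller than 20 points. A non-significant P-value answers neither yes nor no to the second question, because the interval around the estimate may still contain 20 points.

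The planned effect measures do not close the gap. A risk ratio cannot be set against an absolute margin without the base rate: a ratio of 2.0 is 10 points when the follow-up rate is 10%, and 20 points when it is 20%.

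What is at stake is the main conclusion. The investigators expect no important difference, and the Discussion attaches a consequence for practice to not demonstrating one. The plan does not separate a result that excludes a 20-point benefit from one that is merely too imprecise to show a benefit.

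**Working it through.** **Inputs.** From section 2.12: 30% (bolus), 10% (follow-up), two-sided alpha .05, power 80%, 62 per group, margin 20 points. Other true rates below are assumptions, since the article says no reliable data exist.

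**Step 1. Reproduce the plan's figure.** Superiority test of two proportions, pooled variance under the null, no continuity correction, mean rate 0.20:

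n = [1.96·√(2·0.20·0.80) + 0.8416·√(0.30·0.70 + 0.10·0.90)]² / 0.20²
= [1.1087 + 0.4610]² / 0.04 = 61.6, so 62 per group.

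This matches exactly, and power at 62 is 80.3%. The sample size is therefore a superiority calculation.

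**Step 2. One possible result.** Bolus 14/62 = 22.6%, follow-up 6/62 = 9.7%, difference 12.9 points.
- Pooled rate 20/124 = 0.1613. SE = √(0.1613·0.8387·2/62) = 0.0661. z = 0.1290/0.0661 = 1.953, P = .051.
- Newcombe 95% CI, built from the Wilson limits (0.1396 to 0.3441 and 0.0451 to 0.1955):
  - lower = 0.1290 - √[(0.2258 - 0.1396)² + (0.1955 - 0.0968)²] = -0.002
  - upper = 0.1290 + √[(0.3441 - 0.2258)² + (0.0968 - 0.0451)²] = 0.258

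The CI is -0.2 to 25.8 points: not significant, yet a 20-point benefit is not excluded. A second example, 19/62 against 12/62, gives P = .15, a difference of 11.3 points and a CI of -4.0 to 25.9.

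**Step 3. How often this happens.** Every pair of binomial outcomes at 62 per group was enumerated, with the uncorrected chi-square test and the Newcombe 95% CI (unadjusted for strata). The second and third columns are shares of all trials.

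| True rates, bolus / follow-up | Non-significant | Non-significant and upper limit ≥ 20 points | Upper limit < 20 points |
|---|---|---|---|
| 30% / 10% | 19% | 16% | 3% |
| 25% / 10% | 40% | 29% | 12% |
| 30% / 20% | 75% | 49% | 27% |
| 30% / 30% | 95% | 28% | 70% |
| 20% / 20% | 95% | 17% | 80% |
| 10% / 10% | 95% | 4% | 94% |

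**Step 4. What the margin comparison could deliver at 62 per group.** The last column gives the chance of excluding 20 points. It reaches 80% when both true rates are about 20% or lower, falls to 70% when both are 30%, and to 27% when a true 10-point benefit exists (30% against 20%). The first three rows all have a real bolus benefit, so exclusion should be less likely there.

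**Step 5. Why two separate statements are needed.** 6/62 against 0/62 gives a CI of 1.9 to 19.5 points, which lies above zero and below 20. 15/62 against 6/62 gives P = .031, a difference of 14.5 points and a CI of 1.2 to 27.5, which lies above zero but does not exclude 20. Whether the interval excludes 0 and whether it excludes 20 are different questions.

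**The case against.** The strongest reply is that section 2.12, taken alone, is a coherent superiority design: the bolus has to show a gain of 20 points to justify its use, and the sentence in the Introduction only records what the investigators expect. That reading is available, and it is why restating the hypothesis is a legitimate repair. It does not remove the mismatch, because the Introduction puts the claim as the trial's hypothesis and the Discussion draws a consequence from improvement not being demonstrated.

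A second reply is that the information is not lost. Crude rates in both arms will be reported and the de-identified data published, so a reader can compute a crude risk difference and its interval. This stands. What is missing is a prespecified adjusted interval and a rule for reading it.

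A third is that this is a pilot with a physiological endpoint. Yet it is powered on that endpoint and claims relevance to practice.

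Stronger readings are tempting, but the article does not support them:

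- A reader might infer that P > .05 will be taken as proof of no benefit. The article never says so. The Discussion speaks of clinically meaningful improvement, not significance, and only of helping to avoid unnecessary fluid.
- A reader might infer that a significant effect below 20 points has no interpretation. Section 2.12 gives one: it falls short of the minimum worthwhile difference.
- A reader might infer that the sample size is wrong. It reproduces exactly for the superiority question that it addresses.

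**Conclusion.** The point holds as a mismatch between the hypothesis and the inference. The hypothesis carries an absolute 20-point margin, while the primary analysis tests against zero on relative measures and plans neither a risk difference with its interval nor a rule against 20 points.

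Its size depends on the unknown true rates. The share of all trials that would be non-significant without excluding 20 points is 16% at the design rates (30% and 10%), 29% at 25% and 10%, and 49% at 30% and 20%. With no true difference it is 4%, 17% or 28% at common rates of 10%, 20% or 30%. These figures assume 62 analysed per group, an unadjusted chi-square test and Newcombe intervals; the stratified analysis will differ somewhat.

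This does not mean that the trial cannot address its question. The data will allow it, with good precision if rates are low and less if they are around 30%. The rule for reading them should be set before analysis.

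**What to change.** In section 2.11.2:

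1. Add the stratification-adjusted risk difference for the primary outcome (bolus minus follow-up) with its 95% CI in the ITT population.
2. State that the hypothesis in the Introduction is supported only if the upper limit is below 20 points, and that the result is inconclusive for the hypothesis if the interval includes 20 points.
3. Report separately whether the interval excludes 0, so that a result can be statistically above zero yet below the clinically significant level.
4. Keep OR and RR as supportive, and the per-protocol analysis as sensitivity only, in line with section 2.11.1.

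In section 2.12, put the probability of excluding 20 points next to the 80% superiority power, with the true rates labelled as assumptions: about 94%, 80% and 70% if both arms are truly at 10%, 20% or 30%, but only about 27% if the truth is 30% against 20%.

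The alternative is to restate the hypothesis in the Introduction as superiority and temper the Discussion, so that not demonstrating improvement is not linked to a change in practice.

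The cost is wording and one added estimate, with no extra patients. The downside is that some results otherwise read as no difference will be called inconclusive.

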## METHODS

2

### Trial design and setting

2.1

The RESPONSE trial is an investigator‐initiated, open, randomized, controlled, pilot study conducted in two Finnish centers; two intensive care units (ICUs) in Helsinki University Hospital (Helsinki) and in the ICU of Central Finland Central Hospital (Jyväskylä).

### Trial registration

2.2

The RESPONSE trial was registered in the clinicaltrials.gov registry (identifier NCT02860572) on 9 August 2016.

### Trial conduct

2.3

The study protocol has been prepared in accordance with the Standard Protocol Items: Recommendations for Interventional Trials (SPIRIT) guidelines.^17^ The study will be conducted according to the Declaration of Helsinki and its later amendments and according the Good Clinical Practice guidelines.

### Randomization

2.4

Eligible patients will be randomized 1:1 within 1 hour of full eligibility using computer‐based algorithm created by an independent statistician and web‐based allocation concealment for randomization. Randomization is stratified according to the presence/absence of AKI (defined by KDIGO criteria^4^) and sepsis (according to the Sepsis definition^18^). Permutated blocks of varying size (4, 6, or 8) are used.

### Blinding

2.5

Due to the nature of the study, blinding of the ICU personnel is not feasible. The allocation is blinded for the statistician conducting the data analysis. Additionally, we will write an abstract of study results prior to becoming aware of the group allocation and will include this abstract in the appendix of the original publication. Use of randomization blocks of varying size not known for clinicians prevents knowledge of treatment allocation before randomization.

### Inclusion and exclusion criteria

2.6

All admissions to ICU will be screened. If the initial (static) inclusion or exclusion criteria (marked with asterisk) are not excluding the patient becoming eligible for randomization if oliguria develops, the patient will be followed further. If oliguria develops, the presence of dynamic exclusions will be rechecked, and if none of those is present, patient is eligible for randomization.

#### Inclusion criteria

2.6.1

Age over 18*Emergency admission to an ICU*Mean arterial pressure (MAP) >65 mm Hg (with vasopressors if needed) and initial fluid resuscitation for shock/hypovolemia has been givenOliguria (urine output less than 0.5 mL/kg/h) for at least two consecutive hours

#### Exclusion criteria

2.6.2

Marked fluctuations in hemodynamics within the last 2 hours (cardiac arrhythmias, increase in norepinephrine dose over 0.2 µg/kg/min, initiation of inotrope/inodilator)Administration of furosemide within last 6 hoursChronic kidney disease (estimated pre‐critical illness GFR < 60 mL/min/1.73 m^2^)*Renal replacement therapy*Urgent indications for commencing renal replacement therapy for AKIFluid overload (cumulative fluid accumulation exceeds 10% of baseline body weight)^13^
Pulmonary edema (bilateral infiltrates in chest x‐ray)Active bleeding (need for transfusion, platelets, or fresh frozen plasma)Suspected or known intra‐abdominal hypertension (IAP > 16 mm Hg)Pregnant or lactating*Expected survival less than 24 hoursObtaining informed written consent is not possible/ consent is denied

The detailed definitions of inclusion and exclusion criteria are presented in the Supplement.

### Trial interventions

2.7

The timeline of eligibility, randomization, and study interventions are presented in Table 1. The intervention period lasts 2 hours.

**TABLE 1 aas13599-tbl-0001:**
[figure not shown]
Overview of the schedule of enrollment, interventions, and assessments according to the SPIRIT 2013 statement

Abbreviations: AKI, acute kidney injury; CRT, capillary refill time; RRT, renal replacement therapy.

#### Intervention group (noninterventional follow‐up)

2.7.1

Patients in the intervention group will not receive fluid bolus or diuretics to increase urine output during the 2‐hour intervention period.

#### Standard group (fluid bolus group)

2.7.2

Patients will receive 500 mL intravenous crystalloid (Ringer's acetate) infused over 30 minutes using an infusion pump.

#### Concomitant treatment

2.7.3

In both groups, the infusion rate of all on‐going infusions such as nutrition and maintenance fluids will be kept constant during the 2‐hour period. Vasoactive drugs, short‐acting insulin, sedation, and other medications can be titrated according to the discretion of the clinician. No diuretics during the 2‐hour study period are allowed. Modifying the targeted mean arterial pressure (MAP) and adjusting vasopressor dose accordingly (higher MAP potentially increasing urine output^19^) are not recommended in either of the groups.

If severe hemodynamic instability develops during the 2‐hour study period due to suspected hypovolemia (defined as a need to increase norepinephrine‐infusion >0.2 µg/kg/min from baseline or heart rate increase >30 beats/min from baseline), a rescue bolus of 500 mL crystalloid over 30 minutes in both groups can be administered according to the decision of the treating clinician.

### Outcome measures

2.8

#### Primary outcome measure

2.8.1

The primary outcome is defined the individual mean cumulative 2‐hour urine output (mL/kg/h) 2 hours after randomization divided by the mean cumulative 2‐hour urine output (mL/kg/h) measured 2 hours preceding randomization expressed as a percentage (Figure 1). Based on a previous prospective cohort study, we consider doubling of the urine output as a clinically significant increase in urine output among oliguric patients,^20^ if urine output increases at least 10 mL/h (ie difference between cumulative 2‐hour urine output post‐randomization vs pre‐randomization is at least 20 mL).^21^ The proportion of patients who doubled their urine output in both groups will be compared.

**Figure 1 aas13599-fig-0001:**
[figure not shown]
Schematic presentation of determination of urine output for the primary endpoint variable. UO, urine output

Choosing the 2‐hour timeline for the endpoint was based on assumption that urine output in response to fluid bolus would increase in that time based on previous studies.^22^, ^23^, ^24^ In studies among healthy volunteers, the median/mean time to micturition after a large crystalloid bolus (saline 1 liter of over 30 minutes or 30 mL/kg administered 100 mL/min) has been 82‐112 minutes.^22^, ^23^ Moreover, 2‐hour cumulative urine output in response to Furosemide stress test performed best in predicting worsening of AKI.^24^

